### 2.6. Intervention and comparator

#### Overview.

Participants will be randomised to one of two home-based exercise programs while continuing to receive their usual care: (1) an AI-supported TR intervention or (2) a paper-based exercise program serving as the comparator. The intervention period for both groups will be 10 weeks, and in line with current recommendations [26], participants will attend two sessions per week, each lasting 30–45 minutes, for a total of 20 sessions per participant.

Prior to the first at-home session, an in-person physiotherapy assessment will focus on the personalized exercise prescription and detailed instruction on the assigned delivery method (AI TR or paper-based).

Adherence and compliance with the exercise prescription will be monitored throughout the intervention period using an exercise logbook that captures details based on the FIIT-VP principles (frequency, intensity, time, type, volume, and progression) [27].

As usual, care varies across participating countries; all participants will be asked to complete a diary documenting any exercise or physical activity performed outside the study.

Every week, each participant will receive a text message to address technical issues, monitor for adverse events, remind them to fill out their log, and motivate them. In weeks two and six of the project, each participant will receive a phone call to adjust the exercise program accordingly. To promote retention, participants will receive regular contact throughout the study, including weekly text messages and scheduled telephone calls. Flexible scheduling of assessments, individualized exercise progression, and technical support for the telerehabilitation platform will be provided as needed.

#### Intervention: Telerehabilitation (TR) Program.

The telerehabilitation arm will utilize the AI-driven Wizecare^TM^ digital platform (https://www.web.wizecare.com/platform), a commercially available system designed for remote physical therapy and home-based exercise training. WizeCare^TM^ provides access to over 800 exercises (103 Move AI exercises) that target the strength, balance, coordination, and flexibility of the lower limbs, upper limbs, and core. Exercises will be prescribed by physiotherapists according to evidence-based guidelines for individuals with MS [28] and the physiotherapist’s clinical reasoning, and will include approximately 8–10 exercises tailored to the individual’s functional status and needs.

To ensure consistency across sites, exercise prescription will follow a common intervention framework developed by the consortium. Exercise programs will include a combination of lower-limb strengthening, balance, and mobility exercises, with individual tailoring based on participants’ functional status. Progression of exercises will be guided by participant performance, perceived exertion, and safety considerations. Prior to study initiation, all physiotherapists will receive training on the study procedures and intervention framework. Intervention fidelity will be supported through regular consortium meetings and periodic review of exercise prescriptions and participant logs across sites.

A key technological component of the system is MoveAI (patent no. US 11,636,777 B2), which enables motion detection, tracking, and analysis through the built-in camera of a smartphone, tablet, or PC. This allows real-time feedback and guidance without the need for dedicated wearable sensors. The platform complies with international security and privacy standards, including ISO/IEC 27001:2013, ISO 27799:2016, and AMAR 29460001.

Using computer vision technology, MoveAI tracks participant movements during exercise and compares performance against predefined movement parameters. The system provides real-time feedback regarding exercise execution, movement quality, range of motion, and repetition completion, thereby supporting independent exercise performance. In addition, exercise completion and engagement metrics are automatically recorded, allowing clinicians to remotely monitor adherence and progression. AI-enabled telerehabilitation systems have emerged as a promising approach to enhance accessibility, personalization, and monitoring of rehabilitation interventions delivered in the home environment.

Participants will perform asynchronous home-based exercise sessions without the physiotherapist’s input. Ongoing adherence and compliance will be captured automatically through the WizeCare platform and through the written exercise logbook, where participants note the amount of exercise performed and rate their perceived exertion.

#### Comparator: Paper-Based Exercise Program.

Participants randomized to the comparator group will receive a paper-based, individualized home exercise program immediately after their baseline assessment. As in the TR arm, exercises will be prescribed according to evidence-based guidelines for individuals with MS and the physiotherapist’s clinical reasoning and will include approximately 8–10 exercises tailored to the individual’s functional status and needs. Participants will conduct all exercise sessions independently at home, following the written instructions. Adherence will be monitored through the written exercise logbook, where participants note the amount of exercise performed and rate their perceived exertion.

### 2.7. Outcomes

The ***primary clinical outcome*** of the trial is lower-limb functional performance, assessed using the 30-Second Sit-to-Stand Test (30STS). This test was selected as it represents a weight-bearing activity relying on balance, coordination, and muscle strength/power (predominantly lower extremity). Moreover, the majority of exercises in the trial target lower-limb muscle groups similarly. During the 30STS, participants rise from a standard chair without armrests as many times as possible within 30 seconds, with the total number of repetitions recorded as the score. The 30STS has demonstrated strong validity and reliability in pwMS [29]. The primary outcome will be assessed at baseline (T0) and at the end of the 10-week intervention period (T1).

To characterize the study sample, a set of descriptive and clinical measures will be collected at T0, including sex, age, height, body mass, time since MS diagnosis, MS subtype (i.e., relapsing–remitting, secondary progressive, or primary progressive), medication use, comorbidities, disability status (EDSS or PDDS), and use of walking aids (cane, crutches, or rollator). Digital literacy will also be assessed at baseline using the Digital Literacy Scale [30].

***Secondary clinical outcomes*** will be assessed at T0 and T1. Mobility and balance will be evaluated using the Short Physical Performance Battery (SPPB), consisting of standing balance tests, walking speed, and repeated chair rises [31,32], the MiniBESTest [33–35], and the Functional Reach Test (FRT) [36,37]. Walking performance will be measured using the Timed 25-Foot Walk Test (T25FWT) [38,39] and the Six-Minute Walk Test (6MWT) [40]. Cognitive function will be assessed with the Symbol Digit Modalities Test (SDMT) [41].

A range of patient-reported outcomes will be collected at both T0 and T1. These include the MSIS-29 for the physical and psychological impact of MS [42], the Modified Fatigue Impact Scale (MFIS) for fatigue [43], the Multiple Sclerosis Walking Scale–12 (MSWS-12) for perceived walking limitations [44], the State-Trait Anxiety Inventory (STAI) for anxiety [45], the Quick Inventory of Depressive Symptomatology (QIDS) for depressive symptoms [46], and the EQ-5D-5L for health-related quality of life [47]. All participants will complete a semi-structured interview exploring usability, satisfaction, and experiences with the trial process, providing qualitative insights that complement the quantitative outcomes.

An ***economic evaluation*** will be performed from both health-system and societal perspectives. The economic evaluation methodology, data collection procedures, and resource-use measures were developed with input and guidance from a health economics expert within the PLATINUMS consortium to ensure the appropriateness of the proposed approach. Participant-level resource use, including healthcare and social care contacts, informal caregiving, productivity loss, medication use, assistive devices, and out-of-pocket expenses, will be assessed using an adapted Client Service Receipt Inventory (CSRI) [48]. Provider and system-level costs (e.g., platform setup, operational resources, staff training, therapist time, clinical space, administrative support, printed materials) will be captured using standardized implementation cost forms. Quality-adjusted life years (QALYs) will be derived from EQ-5D utilities using the area-under-the-curve method, and costs and QALYs will be compared between study arms to compute the Incremental Cost-Effectiveness Ratio (ICER) [49].

Feasibility of the trial. To assess the feasibility, we will evaluate 1) recruitment and retention rates, 2) evaluation of data collection procedures, 3) evaluation of acceptability of the interventions and study procedures, 4) evaluation of the ability of the consortium to manage the study, 5) safety of the interventions, and 6) preliminary measures of effectiveness of participant responses to the intervention.

When evaluating recruitment rates, we will determine whether 8 months is an acceptable time frame for recruiting 96 participants across 4 sites. To evaluate the data collection and intervention procedures, our semi-structured interviews with participants in each country will help us determine them. For the intervention’s acceptability, we consider an 85% retention rate acceptable and will explore this further in the semi-structured interviews. Furthermore, we will use the Telehealth Usability Questionnaire (TUQ) [50] to assess the usability of the TR system. Trial management will be overseen by an external advisory board. Adverse events (AEs) will be closely monitored throughout the study period, and rates will be compared with those in other exercise intervention studies [51].

Finally, the study will assess multiple outcomes to evaluate the intervention’s preliminary effect, and adherence of ≥ 80% and compliance with the intervention of ≥ 75% are considered acceptable to proceed to a full trial (Fig 1) [52].

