In another systematic review investigating the effects of TR on quality of life in pwMS, TR was found to be more effective than no intervention and as effective as in-person treatment [16]. The review included 12 randomized controlled trials (RCTs), with different types of TR interventions (4 video-based interventions, 3 app-based interventions, 2 augmented reality interventions, 1 virtual reality intervention, 1 video-based intervention with focus on motor imagery, along with an app, and 1 study did not define their TR). Of the studies included, 4 had an exercise component (according to the definition by Caspersen et al. [17]) in their interventions, including pelvic floor muscle training [18,19], resistance and balance training [20], or Pilates [21].

However, despite the numerous potential benefits of TR, several limitations, such as the need for specialist equipment, complex technical solutions, technical difficulties, and lack of digital literacy, may currently prevent its widespread adoption in the MS population. Furthermore, most studies conducted have relatively small sample sizes, do not provide direct feedback to participants, and mainly report patient outcomes, with few investigating lower limb strength, balance, and walking outcomes [22].

A potential way to provide direct feedback to participants is to use a platform that applies artificial intelligence (AI). The platform (WizeCare™) used in the present study can be accessed on either a phone or a computer, with no other devices required. The platform allows direct contact between the participant and therapist using the devices’ built-in cameras. Furthermore, it will use AI software to provide direct feedback to the participant and will allow the therapist to continuously monitor adherence and compliance to the program, as well as movement quality.

Therefore, we aim to examine feasibility and preliminary effectiveness in a multinational, pilot RCT trial comparing AI TR with a paper-based, home-based exercise program. We hypothesize that the AI TR program will be superior to the paper-based exercise program in improving performance on the 30 STS test. Additionally, the RCT will include an economic evaluation to determine the cost-effectiveness of the TR system.

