### 2.5. Randomization

Participants who meet all eligibility criteria and complete the baseline evaluation will be randomly assigned at each site in a 1:1 ratio to either the TR intervention group or the paper-based exercise group. A computer-generated randomization sequence stratified by study site will be used. Randomization procedures at all sites will be coordinated according to a common study protocol developed by the project team. Allocation concealment will be ensured using sequentially numbered, opaque, sealed envelopes prepared and maintained locally at each participating site. Envelopes will be opened only after eligibility has been confirmed and baseline assessments have been completed.

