### 2.9. Sample size

As this study is a pilot feasibility RCT, one aim is to assess feasibility, refine study procedures, and obtain preliminary estimates of variability to inform sample size for a future definitive RCT. Accordingly, the sample size is based on methodological guidance for pilot studies rather than on a formal power calculation. Following the stepped rule-of-thumb proposed by Whitehead et al.[54], approximately 12 participants per arm (i.e., 24 participants in total) are recommended for early-stage pilot trials with continuous outcomes and small to medium expected effect sizes. In line with this guidance, 24 participants per country (a total of 96) will be recruited for the study. If needed, data can be analyzed separately by country. This sample size is expected to provide sufficient information on feasibility metrics, acceptability of study procedures, and change in the primary outcome.

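### The QALY comparison names no adjustment for baseline utility, which makes up half of each two-point QALY; with 41–48 per arm, chance imbalance can reverse the sign of a small incremental QALY

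*Protocol article*

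**What the plan says.** The Introduction says that "the RCT will include an economic evaluation to determine the cost-effectiveness of the TR system". Section 2.7 (Outcomes) gives the recipe in one paragraph. On construction: "Quality-adjusted life years (QALYs) will be derived from EQ-5D utilities using the area-under-the-curve method". On the contrast and its summary: "costs and QALYs will be compared between study arms to compute the Incremental Cost-Effectiveness Ratio (ICER".

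On timing, the same section says "A range of patient-reported outcomes will be collected at both T0 and T1", and EQ-5D-5L is in that list. No other utility measurement is described. Section 2.6 (Overview) says "The intervention period for both groups will be 10 weeks".

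The Statistical Analysis Plan part of section 2.11 covers feasibility, baseline and clinical outcomes. It gives no model for QALYs or costs. Section 2.5 stratifies randomisation by site only.

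**The concern.** With two measurements, the area under the curve is the mean of the T0 and T1 utilities multiplied by the follow-up time. Treatment cannot affect the T0 half. A plain difference in mean QALYs therefore carries any chance T0 difference straight into the denominator of the ICER, and also carries the part of that difference that persists to T1.

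Nothing else in the article removes this. The mixed model in section 2.11 treats T0 and T1 as separate observations per participant. A QALY is one value per participant with T0 already inside it, so that model does not supply the adjustment. Stratifying by site does not balance utility.

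At stake is the direction of the economic result. For a given cost difference, a change of sign in the incremental QALY moves the result to another quadrant of the cost-effectiveness plane, and the ICER is the only summary that the article names.

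**Working it through.** **Inputs from the protocol article**
- Sample size (section 2.9): "24 participants per country (a total of 96) will be recruited for the study". Reproduced as 12 per arm × 2 arms × 4 countries = 96. This rests on a pilot rule of thumb, so there is no power formula to check.
- Allocation (section 2.5): "randomly assigned at each site in a 1:1 ratio", so 48 per arm.
- Retention (section 2.7): "we consider an 85% retention rate acceptable", so 0.85 × 48 = 40.8, about 41 per arm with T1 data if losses are equal.
- Follow-up: T = 10/52 = 0.1923 years.

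**Assumptions, none of them in the article**
- Utility SD 0.15–0.25, equal at T0 and T1.
- T0–T1 correlation ρ 0.5–0.8.
- True T1 utility difference d = 0.05, with 0.03 and 0.10 as alternatives.

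**Formulas** (n per arm)
- QALY per participant = T(u0 + u1)/2.
- True incremental QALY = T·d/2. For d = 0.03, 0.05 and 0.10 this is 0.0029, 0.0048 and 0.0096.
- SE of the baseline imbalance = SD·√(2/n). An imbalance b shifts the unadjusted QALY difference by T·b·(1 + ρ)/2.
- Unadjusted SE = (T/2)·SD·√(2 + 2ρ)·√(2/n).
- SE adjusted for baseline utility = (T/2)·SD·√(1 − ρ²)·√(2/n).
- Variance ratio, adjusted to unadjusted = (1 − ρ²)/(2 + 2ρ) = (1 − ρ)/2. It needs no assumed SD or effect. It is 0.25 at ρ = 0.5 and 0.10 at ρ = 0.8, so adjustment removes 75–90% of the variance and cuts the SE by a factor of 2.0 to 3.2.
- Wrong-sign risk = Φ(−(T·d/2)/SE).

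**One case in full** (SD 0.20, ρ 0.7, n = 48, d = 0.05). The SE of the imbalance is 0.20 × √(2/48) = 0.0408. A one-SE imbalance shifts the QALY difference by 0.0962 × 0.0408 × 1.7 = 0.0067, against a true gain of 0.0048, a ratio of 1.39. The SE is 0.0072 unadjusted and 0.0028 adjusted. The wrong-sign risk is 25% and 4%.

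**Range for d = 0.05**

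| SD | ρ | n per arm | SE unadjusted | SE adjusted | Wrong sign, unadjusted | Wrong sign, adjusted |
|---|---|---|---|---|---|---|
| 0.15 | 0.5 | 48 | 0.0051 | 0.0025 | 17% | 3% |
| 0.15 | 0.8 | 48 | 0.0056 | 0.0018 | 20% | 0.3% |
| 0.20 | 0.7 | 41 | 0.0078 | 0.0030 | 27% | 6% |
| 0.25 | 0.5 | 41 | 0.0092 | 0.0046 | 30% | 15% |
| 0.25 | 0.8 | 41 | 0.0101 | 0.0032 | 32% | 7% |

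**Other effects, same ranges of SD, ρ and n**

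| d | Imbalance shift larger in size than the effect | Wrong sign, unadjusted |
|---|---|---|
| 0.03 | 51–76% | 29–39% |
| 0.05 | 28–61% | 17–32% |
| 0.10 | 3–31% | 3–17% |

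At d = 0.10 the adjusted wrong-sign risk is under 2%.

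**Role of the horizon.** T multiplies both the effect and the imbalance shift. The ratio of 1.39 above is the same at 10, 26 and 52 weeks.

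**The case against.** The strongest objection is that the article does not say the comparison is unadjusted. Comparing arms is compatible with a regression on arm and baseline utility, and area under the curve describes how a participant's QALY is built, not how the arms are contrasted. A condensed article commonly leaves the economic model to a fuller plan, which is not shown, and section 2.7 reports input from a health economics expert. This stands: a reader might infer a decision not to adjust, and the text does not support that. What remains is that the article does state the construction, the contrast and the summary ratio, and the stated comparison can be made much more precise with a value already collected.

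A second objection concerns weight. This is a pilot. Cost-effectiveness is not among the six feasibility items or the adherence and compliance thresholds for proceeding, and the Discussion says the trial is not powered for efficacy and that clinical trends will be read cautiously. That limits the consequence. It does not remove it, because the Introduction still sets the aim of determining cost-effectiveness and the caution is worded for clinical trends.

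Third, every magnitude except the variance ratio rests on assumed utilities. That is correct, and it is why ranges are given.

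**Conclusion.** The point holds as a free improvement in precision. Under the stated assumptions with d = 0.05, the wrong-sign risk is about 17–32% without adjustment and 0.3–15% with it. The 75–90% reduction in variance depends only on ρ of 0.5–0.8 and on equal SDs at the two times.

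Three stronger readings are tempting and are not supported:
- That chance imbalance outweighs any plausible effect. At d = 0.10 it exceeds the effect with a probability of only 3–31%.
- That the short follow-up is the cause. Duration cancels; the cause is the two-point area under the curve combined with small arms.
- That the unadjusted difference is biased. Randomisation keeps it unbiased on average. The problem is imprecision, and bias conditional on the imbalance that happens to occur.

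Adjustment lowers the risk of a wrong sign but does not abolish it, so uncertainty has to be shown in either case.

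**What to change.** Add to the economic paragraph of section 2.7, or to section 2.11, that incremental QALYs will be estimated by regression on arm, baseline EQ-5D-5L utility and site, and that intervals for incremental QALYs and incremental costs will be shown beside any ICER. If a fuller economic plan already says this, one sentence pointing to it is enough.

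Adjust costs for baseline CSRI cost only if the CSRI is collected at T0; the article gives no time point for it. Reporting net monetary benefit over a range of thresholds, and calling the evaluation preliminary, would help but are optional.

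The cost is wording only: EQ-5D-5L at T0 and site are already recorded. Section 2.14 says recruitment has not begun, so fixing the model now also avoids a later choice between adjusted and unadjusted results.

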**Fig 1 pone.0355376.g001:**
[figure not shown]
Participant timeline- schedule of enrollment, interventions, and assessments. Abbreviations: SPPB: Short Physical Performance Battery, FRT: Functional Reach Test, T25FWT: Timed 25 Feet Foot Walk Test, MINIBEStest: Mini Balance Evaluation Systems Test, 6MWT: Six-minute Walk Test, SDMT: Symbol Digit Modalities Test, MSIS-29: 29-Item Multiple Sclerosis Impact Scale, MFIS: Modified Fatigue Impact Scale, MSWS-12: 12-Item Multiple Sclerosis Walking Scale, EQ-5D-5L: EuroQol 5 Dimensions 5 Levels, STAI: State-Trait Anxiety Inventory, QIDS: Quick Inventory of Depressive Symptomatology, TUQ: Telehealth Usability Questionnaire, SSI: Semi-structured interview.

### 2.8. Harms and Adverse Events

Although no significant risks are anticipated in this study, the TR group may have a higher risk than the group doing exercises based on paper-based instructions. Also, as approximately 50% of pwMS experience falls, it cannot be omitted that some participants may fall during the intervention period [53]. The exercise programs included in both intervention arms consist of movements commonly used in physiotherapy for pwMS and are not expected to cause harm. For participants new to exercise and/or being deconditioned due to long-term physical inactivity, transient muscle soreness may occur, particularly the day after training. This response is considered normal and is not regarded as an adverse event.

To minimize the risk of falls or injury during home-based practice, the physiotherapist will provide individualized instructions on how to arrange a safe exercise environment, including guidance on supports, suitable flooring, adequate space, and removal of potential hazards. Participants will also be encouraged to take rest breaks as needed, especially in cases of fatigue or overheating, and to stop exercising if they feel unwell. All adverse events, regardless of severity or suspected relation to the intervention, will be systematically recorded and monitored throughout the study.

